## Abstract

**Background:**

Most studies reporting treatment outcomes for eating disorders at higher levels of care focus on anorexia nervosa and bulimia nervosa. No studies have been published with a singular focus on examining treatment outcomes for adults receiving residential programming specifically designed for the treatment of binge eating spectrum disorders (BESD), including binge eating disorder and bulimia nervosa.

**Objective:**

The purpose of this paper is to outline the protocol of a prospective study examining treatment outcomes at discharge and 3-month, 6-month, and 12-month postdischarge follow-up, for a sample of consecutive admissions to a residential program specifically for patients with BESD.

**Methods:**

One hundred consecutive admissions to a binge eating treatment program were enrolled in the prospective single-arm trial between January 2019 and February 2020. Data were collected at admission, discharge, and 3, 6, and 12 months postdischarge, with admission, discharge, and 12-month follow-up as the major timepoints of interest. Results across the major timepoints will be analyzed with mixed effects general linear models.

**Results:**

The primary aim is to assess the impact of the program on eating disordered behaviors at discharge and 12-month follow-up, which are hypothesized to improve as a result of treatment. Secondary hypotheses include improvements on comorbid symptoms, including trauma, depression, and obsessive-compulsive symptoms, as well as improvements on medical indicators of health, including cholesterol and triglycerides, at discharge and 12-month follow-up.

**Conclusions:**

This study may aid in the development of treatment guidelines for patients with BESD at higher levels of care and lend support to having specialty treatment programs for patients with BESD.

**International Registered Report Identifier (IRRID):**

DERR1-10.2196/32270

## Introduction

### Background

Binge eating disorder (BED) is defined as recurrent episodes of binge eating in the absence of compensatory behaviors, accompanied by marked distress regarding the binge eating [1]. Lifetime prevalence rates of BED among adults are 0.85%-1.9% [2,3] and are often associated with psychiatric comorbidity, medical complications, and a BMI over 30 [2,4]. Bulimia nervosa (BN) is characterized by episodes of binge eating accompanied by compensatory behaviors such as self-induced vomiting [1]. Outpatient treatment based on cognitive-behavioral therapy (CBT) is generally recommended for binge eating spectrum disorders (BESD) such as BED and BN [5,6]. There are times, however, when patients require higher levels of care, such as residential treatment, to interrupt severe and enduring eating disordered behaviors.

Residential treatment provides 24/7 care focused on psychological/behavioral interventions (as opposed to medical stabilization, which is the focus of inpatient treatment). A systematic review of 19 residential eating disorder treatment programs reported that only 14% of the reviewed studies included patients with BED [7]. In contrast, patients with anorexia nervosa (AN) were included in all 19 studies, and patients with BN were included in 90% of the studies reviewed. It is possible that results for patients with BED have not been reported as frequently as AN or BN due to BED only being a recognized diagnosis since the publication of the Diagnostic and Statistical Manual of Mental Disorders, Fifth Edition (DSM-5) in 2013 [1]. Alternatively, binge eating may be underreported due to its normalization to some degree [8].

One of the few studies reporting results separately for BED was from a residential treatment program for obesity, examining patients with and without BED at 6-month and 5-year follow-up [9]. At both follow-up points, there were no differences in weight loss between obese patients with and without BED. Patients with BED had significantly worse scores on all psychosocial measures at baseline and 6-month follow-up. Another study found significant reductions in weight after a 5-month stay at a residential eating disorder program in Italy [10].

Outcomes for patients with BN are reported more frequently than outcomes for patients with BED, although BN outcomes are often not reported separately from other eating disorder diagnoses, with results reported for the overall sample instead. Residential programs that have reported results separately for patients with BN often find stability in BMI over time and improvements in eating disorder psychopathology and depression [10-14]. Purging behaviors have been shown to decrease almost completely for patients with BN while in residential treatment [15].

Although there are no widely agreed upon essential elements of residential treatment for BED, in their review of residential programs across eating disorder diagnoses, Peckmezian and Paxton [7] found that 52% of programs used CBT as a treatment modality, whereas 33% used dialectical behavior therapy (DBT) and 19% used acceptance and commitment therapy (ACT). Briefly, CBT emphasizes behavioral change and addressing overvaluation of shape and weight [16], DBT focuses on teaching skills such as mindfulness and emotion regulation [17], and ACT encourages patients to develop psychological flexibility and live in accordance with their values and goals [18].

Most residential programs are generally designed for patients across the eating disorders spectrum. No studies have been published with a singular focus on examining treatment outcomes for adults receiving residential programming specifically designed for the treatment of BESD. The purpose of this paper is to describe the detailed protocol of a study prospectively examining treatment outcomes for a sample of consecutive admissions to a residential program specifically for patients with BESD (BED or BN). Patients with AN – binge/purge subtype (AN-BP) were not included in the binge eating disorder treatment program described in this paper, given the need for a different treatment focus for this patient population, including weight restoration.

### Primary Hypotheses

It is hypothesized that meaningful improvements (defined here as pre- to posttreatment change with at least a medium Cohen *d* effect size of 0.5) will be demonstrated on measures of eating disorder psychopathology as a result of treatment addressing binge eating and other disordered eating behaviors. It is also hypothesized that a history of trauma and current posttraumatic stress disorder (PTSD) symptoms will moderate treatment effects, in that improvements in eating disorder symptoms will be less marked among those with a history of trauma or current PTSD symptoms. Although some studies have found that PTSD does not result in poorer treatment outcomes for binge eating [19,20], other studies have found that PTSD predicts more binge eating at end of treatment [21] and premature treatment dropout for patients with BN [22]. Given these mixed findings and the assumed increased level of severity in the current population seeking higher level of care treatment, PTSD will be examined as a moderator.

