### Secondary Hypotheses

It is also hypothesized that meaningful improvements will be demonstrated on a measure of experiential avoidance of weight-related feelings, thoughts, and actions, although no a priori hypotheses are made as to which subscales may improve the most. Depression, dysfunctional attitudes, and quality of life are also expected to meaningfully improve. Small improvements (defined here as pre- to posttreatment change with at least a small Cohen *d* effect size of 0.3) on a measure of obsessive-compulsive symptoms are expected, as addressing obsessive-compulsive symptoms is not a main target for treatment overall in the treatment program, but may be addressed in individual therapy. Anxiety and self-esteem are both hypothesized to meaningfully improve after treatment. Given that the treatment program incorporates trauma-informed care, it is hypothesized that meaningful improvements on a measure of PTSD symptoms will be found. It is also hypothesized that treatment will result in improved levels of triglycerides, high-density lipoprotein (HDL) and low-density lipoprotein (LDL) cholesterol, and glycated hemoglobin (HbA_1c_) due to normalization of eating patterns. It is well established that having a BMI over 30 shortens life and adversely impacts years of productive life [23]. The mechanism for those adverse effects is via contributors to the development of the metabolic syndrome and a heightened cardiac risk profile, such as hyperlipidemia and hyperglycemia. Thus, measuring those variables at baseline and then reassessing their serum values after treatment is one way to define the potential value of this program to reduce cardiac risk. Findings from this study may inform treatment guidelines for patients with BESD receiving treatment at higher levels of care.

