## Methods

### Study Design

This study is a prospective pragmatic single-arm trial with consecutive admissions. As with all pragmatic trials, the primary goal of this study was to observe unbiased patient outcomes in a real-world setting. Given the acuity of patients, and the lack of an evidence-based treatment as usual for patients with BESD at this level of care, it was neither feasible nor ethical to execute a randomized or nonrandomized design with a treatment as usual or nontreatment comparison condition. To minimize bias from retrospective reports and convenience samples, this study was devised prospectively to examine outcomes in 100 consecutive admissions who agreed to participate.

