### A Priori Analytic Plan

All data at admission, discharge, and 3, 6, and 12 months postdischarge will be aggregated for the full sample and examined for patterns of missingness, outliers (>3 standard deviations from mean), and normality of distributions. Our a priori assumptions are that data will be missing at random, and all data will be normally distributed with the appropriately minimal proportion of outlier data points. Mixed models will be used to examine fixed and random effects of linear within-person change in BDI-II, EDQOL, OCI-R, STAI, RSE, DAS-SF, PCL-5, BES, and NEQ across our major timepoints of interest (admission, discharge, and 12-month follow-up). Mixed models will be run both unadjusted, as well as adjusted for person-level variables of BMI at admission, demographic variables of age, race/ethnicity, and gender, and diagnosis. Lastly, to examine the potential for different trajectories within-treatment and posttreatment, nested model comparisons will be conducted comparing the linear mixed models described above with mixed models including a quadratic time variable. Based on an expected effect size of at least *d*=0.5, and to account for a range of potentially inflated intraclass correlation coefficients that could reduce power, a sample size of 100 was determined to be sufficient to test both the mixed effects main effect hypotheses above, as well as the mixed effects 2-level interactions specified below.

All data at each of these timepoints will also be subset by patients above and below the threshold for history of trauma (defined as an ACES score ≥4) and above and below the most commonly established threshold for clinically significant levels of PTSD symptoms via the PCL-5 (PCL-5 ≥33) [48]. These subsets of patients will be compared using independent-samples *t* tests to determine any differences in point-prevalence of BDI-II, EDQOL, OCI-R, STAI, RSE, DAS-SF, BES, and NEQ by history of trauma or current trauma symptoms, and traditional moderation analyses with interaction terms added to the mixed models described above to determine any differences in changes over time of BDI-II, EDQOL, OCI-R, STAI, RSE, DAS-SF, BES, and NEQ by history of trauma or current trauma symptoms.

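### The primary hypothesis is a pre-post change of at least d = 0.5, but the planned linear time effect does not estimate that change or refer to 0.5, and the sample-size sentence supports only a test against zero.

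*Protocol article*

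**What the plan says.** Protocol article, Primary Hypotheses: patients are expected to show "meaningful improvements (defined here as pre- to posttreatment change with at least a medium Cohen" d effect size of 0.5 on measures of eating disorder psychopathology. Secondary Hypotheses sets a lower bar of 0.3 for obsessive-compulsive symptoms: "Small improvements (defined here as pre- to posttreatment change with at least a small Cohen" d. Neither section says which SD standardises the change.

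Study Design: "This study is a prospective pragmatic single-arm trial with consecutive admissions". The Discussion (Principal Findings) concedes that effectiveness is hard to judge without a control group, and offers the prespecified degree of improvement as what may still make the findings useful for treatment guidelines.

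A Priori Analytic Plan: "Mixed models will be used to examine fixed and random effects of linear within-person change" in the listed scales "across our major timepoints of interest (admission, discharge, and 12-month follow-up"). A later sentence adds a nested comparison with a model that includes quadratic time. On sample size, the planning effect is a d of 0.5 or more, an unspecified range of intraclass correlations is said to have been allowed for, and the conclusion is that "a sample size of 100 was determined to be sufficient to test both the mixed effects main effect hypotheses above". The interaction tests are covered by the same statement. The section gives no significance level, power, intraclass correlation value or dropout allowance, and no rule that refers to 0.5 or 0.3.

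**The concern.** The hypothesis and the analysis ask different questions. The hypothesis asks whether the change from before to after treatment is at least half an SD. The analysis asks whether there is a linear trend across three visits, and the default test of that trend is against no change. With no control arm, the size of the change carries the argument, so the route from model output to a verdict on 0.5 matters more here than in a randomised trial.

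The sample-size sentence has the same problem. An effect of 0.5 can be the alternative for a test against zero, or it can be the bar to be cleared. Power computed at 0.5 says nothing useful about clearing a bar of 0.5. A reader who takes the sentence at face value would think the study well powered for the hypothesis as worded.

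**Working it through.** **Inputs.** From the article: threshold 0.5 (0.3 for the OCI-R), expected effect at least 0.5, N = 100, visits at admission, discharge and 12 months after discharge, average stay 30 days. Assumed because not stated: two-sided alpha of 5%, 100 complete pairs, equal SDs at the two visits, and an admission-to-follow-up correlation r of 0.3, 0.5 or 0.7.

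**1. The stated sample size.** N = 100 cannot be derived from the article. As a check, take a paired comparison with d on the SD of change. For 80% power against zero, n = ((1.96 + 0.84)/0.5)² = 31.4, so 32; the t distribution gives 34 (44 for 90%). With n = 100 the noncentrality is 0.5 × √100 = 5 and power is about 99.9%. Sufficient is a fair word for a test of change against zero.

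**2. The same N against the threshold** (d on the SD of change, n = 100).
- If the estimate must reach 0.5, the probability is about 3% at a true d of 0.3, 18% at 0.4, 50% at 0.5 and 83% at 0.6. The 50% does not improve with sample size, because an estimate centred on 0.5 falls below it about half the time.
- If the lower 95% limit must exceed 0.5, the probability at a true d of 0.5 is 2.5%.

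**3. Slope versus contrast.** Suppose patients improve by 0.5 SD at discharge and hold it, so mean improvement is 0, 0.5, 0.5. With complete data, random intercept and slope and independent residuals of equal variance, the mixed-model slope equals the least-squares slope.
- Visits coded 0, 1, 2: slope = (−1×0 + 0×0.5 + 1×0.5)/2 = 0.25 per visit. The discharge mean has zero weight, and the fitted admission-to-discharge change is 0.25, half the true value.
- Months coded 0, 1, 13 (stay taken as one month): the mean is 4.67, the deviations are −4.67, −3.67 and 8.33, and their sum of squares is 104.67. Slope = (−3.67×0.5 + 8.33×0.5)/104.67 = 0.0223 per month. The fitted change is 0.02 over the first month and 13 × 0.0223 = 0.29 at 12 months after discharge, against a true 0.5 at both.

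**4. The denominator.** With equal SDs, d(change SD) = d(admission SD)/√(2(1−r)). A change-SD d of 0.5 is therefore 0.5 × √1.4 = 0.59, 0.5 × 1 = 0.50, or 0.5 × √0.6 = 0.39 admission SDs at r = 0.3, 0.5, 0.7.

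**5. Precision of d on the admission SD.** SE(d) = √(2(1−r)/n + d²/(2n)); the second term comes from estimating the SD. At d = 0.5 and n = 100:

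| r | SE | 95% half-width |
|---|---|---|
| 0.3 | √(0.0140 + 0.00125) = 0.123 | 0.24 |
| 0.5 | √(0.0100 + 0.00125) = 0.106 | 0.21 |
| 0.7 | √(0.0060 + 0.00125) = 0.085 | 0.17 |

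For an 80% chance that the lower limit exceeds 0.5, solve d = 0.5 + 2.80 × SE(d). This gives about 0.87, 0.82 and 0.76 at r = 0.3, 0.5 and 0.7. Check at r = 0.5: 0.5 + 2.80 × √(0.01 + 0.82²/200) = 0.82.

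**The case against.** A reader might infer that a small but significant change will be declared a success, since with 100 pairs a change is significant from about 0.23, 0.20 or 0.15 admission SDs at r = 0.3, 0.5, 0.7. The article does not support that. It nowhere says that p<0.05 alone is enough, and its definition, read literally, rules out an observed d of 0.2 or 0.3 as a meaningful improvement. The separate bar of 0.3 for the OCI-R shows that the authors do distinguish degrees.

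It is also true that a mixed model can yield a d from its contrasts, and that the quadratic model, with three visits, reproduces the three visit means. But that model enters as a comparison of trajectories, and nothing says the pre-post contrast will be taken from it.

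The choice of SD is a detail that an article may leave to a full analysis plan, and one may exist. Taken alone it would not be a finding. It counts here because the decision threshold is stated in the article and the choice moves it.

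Finally, the expected effect is at least 0.5, so the 50% figure is the boundary case, and the article never claims power to place a confidence limit above 0.5. Both points stand. They limit the criticism to what the sample-size sentence can be taken to support.

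**Conclusion.** The point holds in a limited form. The analysis described does not estimate the change that the primary hypothesis is about, and nothing in it ties the verdict to 0.5. The adequacy of N = 100 applies to detecting change from zero (about 99.9% power at 0.5 on the SD of change) and not to the hypothesis as worded, for which the chance of reaching 0.5 at a true 0.5 is about one half under a point-estimate rule. The unstated SD shifts the bar between 0.39 and 0.59 admission SDs over r = 0.7 to 0.3.

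The figures rest on assumed correlations, equal SDs and 100 complete pairs; dropout by 12 months would widen the intervals. The slope illustration assumes an early gain that is held; its size would differ under other trajectories. That a linear slope is in general not the pre-post contrast does not depend on these assumptions.

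**What to change.** - In the mixed model, treat time as categorical and estimate the admission-to-discharge and admission-to-12-month contrasts.
- Define d as the contrast divided by the admission SD, reported with a 95% CI from a patient-level bootstrap.
- Judge each hypothesis on d against 0.5 (0.3 for the OCI-R), not on p against zero, and say whether the CI lies above, includes or lies below the threshold.
- Reword the sample-size sentence: 100 patients are adequate to detect change from zero, and d is estimated to within about ±0.17 to ±0.24 at d = 0.5 (assumed r = 0.7 to 0.3, 100 complete pairs; wider with dropout).
- Requiring the lower limit to clear 0.5 is optional. If adopted, state that the true d must be about 0.87, 0.82 or 0.76 (r = 0.3, 0.5, 0.7) for an 80% chance of success.

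Cost: changes of wording, slightly more analysis work, and a less favourable statement about N = 100. No new patients or data are needed. By the article's timeline data collection is complete and analysis has not begun, so the change can still be made in advance.

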### Secondary Hypotheses

It is also hypothesized that meaningful improvements will be demonstrated on a measure of experiential avoidance of weight-related feelings, thoughts, and actions, although no a priori hypotheses are made as to which subscales may improve the most. Depression, dysfunctional attitudes, and quality of life are also expected to meaningfully improve. Small improvements (defined here as pre- to posttreatment change with at least a small Cohen *d* effect size of 0.3) on a measure of obsessive-compulsive symptoms are expected, as addressing obsessive-compulsive symptoms is not a main target for treatment overall in the treatment program, but may be addressed in individual therapy. Anxiety and self-esteem are both hypothesized to meaningfully improve after treatment. Given that the treatment program incorporates trauma-informed care, it is hypothesized that meaningful improvements on a measure of PTSD symptoms will be found. It is also hypothesized that treatment will result in improved levels of triglycerides, high-density lipoprotein (HDL) and low-density lipoprotein (LDL) cholesterol, and glycated hemoglobin (HbA_1c_) due to normalization of eating patterns. It is well established that having a BMI over 30 shortens life and adversely impacts years of productive life [23]. The mechanism for those adverse effects is via contributors to the development of the metabolic syndrome and a heightened cardiac risk profile, such as hyperlipidemia and hyperglycemia. Thus, measuring those variables at baseline and then reassessing their serum values after treatment is one way to define the potential value of this program to reduce cardiac risk. Findings from this study may inform treatment guidelines for patients with BESD receiving treatment at higher levels of care.

## Methods

### Study Design

This study is a prospective pragmatic single-arm trial with consecutive admissions. As with all pragmatic trials, the primary goal of this study was to observe unbiased patient outcomes in a real-world setting. Given the acuity of patients, and the lack of an evidence-based treatment as usual for patients with BESD at this level of care, it was neither feasible nor ethical to execute a randomized or nonrandomized design with a treatment as usual or nontreatment comparison condition. To minimize bias from retrospective reports and convenience samples, this study was devised prospectively to examine outcomes in 100 consecutive admissions who agreed to participate.

### Participants and Eligibility Criteria

One hundred consecutive admissions to the Binge Eating Treatment & Recovery (BETR) residential program in a large Midwestern city in the United States who consented to participate were enrolled in this study. The BETR program is part of Eating Recovery Center’s (ERC) network of eating disorder treatment programs. ERC is a multisite, national program offering higher levels of care to patients with eating disorders. Treatment is provided by multidisciplinary teams of a physician, licensed psychotherapist, psychiatrist, and registered dietitian, with a focus on evidence-based group therapies. Participants were approached to participate in the study within the first 3 days of their admission date.

Inclusion criteria for patients admitting to the BETR treatment program are the following: (1) age ≥18 years, (2) have binge eating as a predominant symptom associated with their primary or secondary diagnosis at admission, and (3) voluntary consent for treatment from the patient. Patients were recommended for residential level of care (as opposed to partial hospitalization programming) if they had prominent mood and anxiety symptoms (ie, nonsuicidal self-injury, suicidality, sleep disturbance) associated with their eating disorder and/or if they lacked support for recovery in their home environments. Other inclusion criteria included severity of eating disorder symptoms, abnormalities in initial labs, or poorly controlled medical conditions that were exacerbated by eating disorder symptoms (ie, diabetes mellitus), sleep-related disturbances, or nocturnal-related eating. Exclusion criteria that prevented patients from admitting to the BETR treatment program are the following: (1) primary substance use or psychotic disorder, (2) active psychosis, (3) immobility (patients could not be bedbound, and needed to be able to perform activities of daily living independently or with some nursing assistance), (4) high risk for refeeding syndrome or need for refeeding secondary to restriction, due to the lack of capacity for tube feeds/lack of focus on refeeding on the unit, and (5) need for inpatient medical stabilization. Additionally, and without regard to this study, patients are always asked (but never required) to complete a battery of self-report measures at admission and discharge. An additional inclusion criterion for this study was consent to participate in this study in addition to treatment, including providing self-report data and lab draws while in treatment and during follow-up posttreatment. Exclusion criteria for the study were (1) unwillingness to provide informed consent, and (2) the presence of any intellectual disability, cognitive deficit, or physical incapacitation that may have prevented participants from understanding or completing the informed consent process or completing assessment measures.

